### Concomitant dugs and combination therapy

In the event patients are receiving a calcineurin inhibitor (cyclosporine or tacrolimus) at screening, tapering of the drug begins at day 86, with discontinuation by day 169; the dosage will be sequentially reduced every 28 days from day 86 onwards and discontinued on approximately day 169 (Fig. 2). If patients were taking any other immunosuppressive agents (MMF, mizoribine, azathioprine, cyclophosphamide or chlorambucil), these drugs are discontinued by the beginning of RTX administration (day 1) (Fig. 2).

Trimethoprim-sulfamethoxazole is administered from the beginning of RTX treatment (day 1) until the date on which peripheral blood B cell recovery (≥ 5 cells/μL) is confirmed for the prevention of *Pneumocystis jirovecii* infection.

Combination therapy with the following drugs and treatment are prohibited during the clinical trial period.Commercially available rituximab.Immunosuppressive drugs or alkylating agents with an immunosuppressive effect except in the following cases.In the case “cyclosporine, tacrolimus, cyclophosphamide, mizoribine, MMF or chlorambucil” continues to be used from prior to the start of the clinical trial.In the case treatment failure is determined.

## Live vaccines

### The discontinuation of investigational drug administration

Investigators are to discontinue the administration of investigational drugs to participants to whom any of the following circumstances apply:If treatment failure (FRNS, SDNS, or SRNS) is observed during the observation period.If prohibited drug 1.2. (see above) is used as a treatment for nephrotic syndrome.If the participant or legal representative requests discontinuation of the administration of the investigational drug.If the investigators determine the continuation of investigational drug administration to be difficult for any other reason such as the occurrence of adverse events.If the participant becomes pregnant.

### Visit schedule

During the clinical trial period, investigators carry out observations, examinations, and surveys in accordance with the prescribed schedule. The visit schedule is shown in Table 1. Study visits occur every week during the RTX administration period, every 1 month during the first 6 month of the investigational drug administration period, and every 2 month, thereafter. Urine samples and blood samples are taken every visit.

**Table 1 Tab1:** Clinical trial schedule

	Screening period	Observation period				Observation period														Follow-up period
		(Rituximab administration period)				(Investigational drug administration period)														
Day	Within 35 days	1	8	15	22	29	57	85	113	141	169	225	281	337	393	449	505	Relapse	Investigation drug discontinuation	36/48 month Clinical trial discontinuation
Visit		1	2	3	4	5	6	7	8	9	10	11	12	13	14	15	16			
Obtaining informed consent	○																			
Medical examination	○	○	○	○	○	○	○	○	○	○	○	○	○	○	○	○	○	○	○	
Investigation drug administration		○	○	○	○	○	○	○	○	○	○	○	○	○	○	○	○	○	○	
Background survey	○																			
Concomitant drug survey	○	○	○	○	○	○	○	○	○	○	○	○	○	○	○	○	○	○	○	
Height/weight	○	○	○	○	○	○	○	○	○	○	○	○	○	○	○	○	○	○	△	○
Blood pressure	○	○	○	○	○	○	○	○	○	○	○	○	○	○	○	○	○	○	△	○
Pulse, body temperature	○	○	○	○	○	○					○			○			○		△	
Pregnancy test	○																			
HIV, HCV, HBV^a^	○																			
Electrocardiogram	○																○		△	
Chest X-ray	○																○		△	
Relapse evaluation		○	○	○	○	○	○	○	○	○	○	○	○	○	○	○	○	○	○	○
Adverse event evaluation		○	○	○	○	○	○	○	○	○	○	○	○	○	○	○	○	○	○	○
After treatment																				○
Hematological examination	○	○	○	○	○	○	○	○	○	○	○	○	○	○	○	○	○	○	△	
Immunoglobulin examination		○					○		○		○			○			○		△	
Estimated glomerular filtration rate	○	○			○	○					○			○			○	○	○	
Urinalysis	○	○	○	○	○	○	○	○	○	○	○	○	○	○	○	○	○	○	○	○
Peripheral blood B cell count	○	○	○		○	○	○		○		○	○	○	○	○	○	○	○	○	□

△: Conduct if possible

□: Conduct until the peripheral blood B cell recovery (≥ 5/μL) is confirmed

^a^
*HIV* human immunodeficiency virus, *HCV* hepatitis C virus, *HBV* hepatitis B virus

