### Study design and patients

We conduct a multicenter, double-blind, randomized, placebo-controlled trial to assess the efficacy and safety of MMF after RTX therapy in children with complicated FRNS/SDNS (Fig. 1, Table 2 [6]). In total, 80 patients from 27 institutions in Japan will be enrolled in this study. We will diagnose NS and remission and relapse according to the International Study of Kidney Disease in Children (ISKDC) [6, 33]. Patients who are aged between 1 and 18 years old at the time of onset of idiopathic nephrotic syndrome and are aged 2 years or above at the time of registration are eligible if they fall into the complicated FRNS/SDNS category.

Inclusion and exclusion criteria are as follows:

Inclusion criteria:Diagnosed as INS according to the ISKDC criteria.The initial onset of INS is at between 1 and 18 years of age, and the patient is 2 years of age or older at assignment.Patients meeting one of the following criteria:Diagnosed with frequent relapse or steroid dependence and once again diagnosed with frequent relapse or steroid dependence after completion of immunosuppressive drug therapy (cyclosporine, cyclophosphamide, or mizoribine, etc.).Diagnosed with frequent relapse or steroid dependence and once again diagnosed with frequent relapse or steroid dependence during immunosuppressive drug therapy (cyclosporine, cyclophosphamide, or mizoribine, etc.).Diagnosed with steroid resistance following the onset of INS and diagnosed with frequent relapse or steroid dependence during or after the completion of immunosuppressive drug therapy (cyclosporine alone or combination of cyclosporine and methylprednisolone, etc.).Patients with records of the nearest preceding 3 relapses.Patients in whom steroid sensitivity is observed during treatment of relapse immediately prior to assignment.Patients in whom ≥5 CD20-positive cells/μL are observed in the peripheral blood.Patients who can be hospitalized overnight on the first day of rituximab administration.Written informed consent.

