Exclusion criteria:Patients who have been diagnosed with nephritic-NS, such as IgA nephropathy, prior to assignment or in whom secondary NS is suspected.Patients who have used a monoclonal antibody other than rituximab.Patients meeting one of the following infection criteria:Presence or history of severe infections within 6 months prior to assignment.Presence or history of opportunistic infections within 6 months prior to assignment.Presence of active tuberculosis.Patients with a history of tuberculosis or in whom tuberculosis is suspected.Presence or history of active hepatitis B or hepatitis C or hepatitis B virus carrier.Presence of human immunodeficiency virus (HIV) infection.Presence or history of angina pectoris, cardiac failure, myocardial infarction, or serious arrhythmia (findings observed under Grade 4 of the Common Terminology Criteria for Adverse Events (CTCAE)).Presence or history of autoimmune diseases or vascular purpura.Presence or history of malignant tumor.History of organ transplantation.History of drug allergies to methylprednisolone, acetaminophen, or d-chlorpheniramine maleate.Uncontrollable hypertension.Deteriorated kidney function, e.g. estimated glomerular filtration rate (GFR) < 60 mL/min/1.73 m^2^.Having received a live vaccine within 4 weeks prior to enrollment.Patients showing one of the following abnormal clinical laboratory values:Leukocytes < 3000/μL.Neutrophils < 1500/μL.Platelets < 50,000/μL.Alanine aminotransferase (ALT) > 2.5× upper limit of normal value.Aspartate aminotransferase (AST) > 2.5× upper limit of normal value.Positive for hepatitis B surface (HBs) antigen, HBs antibody, hepatitis B core (HBc) antibody, or HCV antibody.Positive for HIV antibody.Patients who do not agree with contraception during the study period.Women during pregnancy or breast-feeding.Judged inappropriate for this study by the treating or study physicians.

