### Dosage regimen

RTX and the investigational drug (MMF or placebo) are administered in this trial. The dosage regimen is shown in Fig. 2. For the RTX plus MMF combination group, RTX is administered as 4 × 375 mg/m^2^ doses (maximum dose: 500 mg) given at weekly intervals and MMF is additionally administered at a dose of 1000–1200 mg/m^2^/day (maximum 2 g/day) twice daily after breakfast and dinner, continued for 17 months after RTX treatment. For the RTX plus placebo group, RTX is administered as 4× 375 mg/m^2^ doses (maximum dose: 500 mg) given at weekly intervals and the placebo is administered in place of MMF.

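### Pregnancy is tested once, at screening, and never again before rituximab, before study drug, or during 476 days of dosing

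*Protocol article*

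**What the plan says.** Visit schedule states that "investigators carry out observations, examinations, and surveys in accordance with the prescribed schedule", and Table 1 is that schedule. Its row "Pregnancy test" has one mark, under screening. There is no mark at visits 1 to 16, at relapse, at drug discontinuation or at follow-up. The same section adds: "Urine samples and blood samples are taken every visit".

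Other sections make pregnancy matter both at entry and throughout:

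- Study design and patients excludes "Women during pregnancy or breast-feeding" and also "Patients who do not agree with contraception during the study period".
- The discontinuation of investigational drug administration lists "If the participant becomes pregnant" among the reasons to stop.
- Allocation key opening provides for urgent disclosure of the code when a participant becomes pregnant and stops study drug.

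The age criterion requires that "the patient is 2 years of age or older at assignment". It sets no upper limit at assignment, and disease onset may be as late as 18 years. Under Dosage regimen, MMF is "continued for 17 months after RTX treatment", with placebo given in its place in the control group.

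**The concern.** The protocol treats pregnancy as a continuing safety condition but schedules a test for it only as an entry check. Post-menarchal participants are eligible, and the contraception and pregnancy criteria show that the sponsor expects some.

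Two consequences follow:

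- A participant who conceives between the screening test and day 1, or between day 1 and day 29, meets an exclusion criterion. She can still receive four rituximab infusions and start study drug, because no scheduled procedure would show it.
- During dosing, an early pregnancy may not be apparent at a visit. Stopping the drug and opening the code then wait for self-report, examination findings, adverse event evaluation or a test done on suspicion.

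**Working it through.** **Is the single mark a real feature of the schedule?** Comparing rows of Table 1:

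| Item | Screening | Visits 1–16 | Drug discontinuation |
|---|---|---|---|
| Pregnancy test | yes | none | none |
| HIV, HCV, HBV | yes | none | none |
| Electrocardiogram | yes | day 505 | if possible |
| Chest X-ray | yes | day 505 | if possible |
| Medical examination | yes | all 16 | yes |
| Adverse event evaluation | no | all 16 | yes |

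The table marks repeats where they are wanted and has symbols for conditional testing; neither appears in the pregnancy row. The viral serology row is also screening-only, but no stopping or unblinding rule depends on those infections. Pregnancy has one of each.

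**Inputs.**

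- Screening window: up to 35 days (Table 1). The reference point is not spelled out; day 1 is the natural reading.
- First rituximab: day 1. End of study drug: day 505 (Observation period).
- Start of study drug: day 29, the first column of the investigational drug period in the Table 1 header. The drug administration row is itself marked from day 1, apparently counting rituximab.

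**Reproducing the stated duration.** 505 − 29 = 476 days, and 476 / 28 = 17. The stated 17 months are thus 28-day months, which supports day 29 as the start.

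**Maximum age of the only scheduled test.**

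- At day 1: 35 days.
- At day 29: 35 + (29 − 1) = 35 + 28 = 63 days.
- At day 505: 35 + (505 − 1) = 35 + 504 = 539 days.

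Twelve visits fall in the study drug period (days 29, 57, 85, 113, 141, 169, 225, 281, 337, 393, 449 and 505), none with a test.

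**Alternative schedules.**

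| Test days added | Tests | Longest interval from day 1 to day 505 |
|---|---|---|
| None (current) | 0 | 504 days (539 counted from the earliest screening test) |
| 1, 29 | 2 | 476 days |
| 1, 29, 85, 141, 225, 337, 449, 505 | 8 | 112 days |
| 1 and all twelve visits from day 29 | 13 | 56 days |

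For the eight-test schedule the successive gaps are 28, 56, 56, 84, 112, 112 and 56 days. The 13-test option leaves out days 8, 15 and 22, which fall between the day 1 and day 29 tests.

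**The case against.** The best defence is that nothing here is contradictory. The screening test serves the entry criterion, and the stopping and unblinding rules apply whenever pregnancy becomes known, whether or not a test was scheduled. Participants must agree to contraception, they are examined and assessed for adverse events at all 16 visits, and nothing forbids testing on suspicion. The article is also condensed, so the full protocol may hold further pregnancy procedures. Finally, elapsed days are not risk: the protocol gives no fetal risk figure and no count of post-menarchal participants, and 35, 63 and 539 are maxima.

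Much of this stands as a limit on size. The safeguards are real, the harm cannot be quantified, and the frequency of testing during treatment is a matter of judgement. A day 505 test also comes too late to prevent exposure to study drug; it can only identify a pregnancy that began during dosing.

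It does not remove the gap. Table 1 is an item-by-visit grid that the text tells investigators to follow, so the single mark is a stated choice rather than detail left to another document. Contraception agreement and examination are not tests, and the stopping and unblinding rules themselves allow for pregnancy despite them. The other specific clinical triggers for stopping, treatment failure and prohibited drug use, have scheduled observations: relapse evaluation, urinalysis and the concomitant drug survey at each visit.

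**Conclusion.** The concern holds. As written, the schedule allows a participant who has become pregnant since screening to be given rituximab and study drug, and it offers no routine means of triggering the protocol's own stopping rule over 476 days of dosing. The finding of no scheduled test at or after day 1 does not depend on how the 35-day window is read. The 35, 63 and 539 day figures assume that the window ends on day 1 and that screening took place as early as allowed. If study drug were taken to start on day 1, the untested dosing span would be 504 days instead of 476.

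This is an inexpensive safety improvement that should be made. It has no bearing on the endpoint, sample size, type I error or analysis, and the expected number of exposed pregnancies cannot be stated from the protocol.

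**What to change.** In the pregnancy row of Table 1, for post-menarchal participants only:

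1. Add a urine test on day 1 before the infusion and on day 29 before the first dose of study drug. These two are the core, because they reconfirm the exclusion criterion before exposure.
2. Add a urine test at every second visit on study drug (days 85, 141, 225, 337 and 449) and one at day 505 or at drug discontinuation. This frequency can be adjusted: the two core tests alone leave 476 days untested, and testing at all visits from day 29 brings the longest gap to 56 days.
3. State that the 35-day screening window is counted back from day 1, if that is what is meant.

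Leave the stopping and code-opening rules as they are.

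The cost is one table row and a line in the consent and assent forms. No visit, sample or invasive procedure is added. The protocol does not give the number of post-menarchal participants. Assuming 5% to 25% of 80, that is 4 to 20 participants, and eight tests each gives at most 4 × 8 = 32 to 20 × 8 = 160 urine tests over the whole trial. The main drawback is the sensitivity of repeated testing in adolescents, which the consent and assent discussion should cover.

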### Allocation key opening

To maintain blinding, the “allocation codes” will be disclosed after the entire clinical trial is completed and all data and determination secured. However, if any of the following circumstances apply, the allocation code of the patient will be urgently disclosed.The participant experiences a serious adverse event that leads to death or is life-threatening.The participant experiences another serious adverse event and it is determined the information is essential in considering the relevant patient’s treatment.There is determined to be treatment failure (FRNS, SDNS or SRNS).The participant becomes pregnant and discontinues the administration of investigational drug.

### Outcomes

The primary endpoint is defined as the time-to-treatment failure (development of frequent relapses, steroid dependence or steroid resistance). Diagnosis of FRNS, SDNS, and SRNS is based on relapse dates according to the ISKDC (Table 2). The secondary end points are time to relapse, relapse rate, time to FRNS, time to SDNS, time to SRNS, total steroid dose, peripheral blood B cell depletion period and adverse events. Adverse events are recorded throughout the trial period and assessed using CTCAE.

**Table 2 Tab2:** Definitions [6]

A. *Nephrotic syndrome*	The presence of a urine protein-to-creatinine ratio of 1.8 or above and serum albumin of 2.5 g/dL or below.
B. *Complicated nephrotic syndrome*	A patient that fulfills any of the following criteria is deemed to suffer from complicated nephrotic syndrome: (1) Diagnosed with frequent relapse or steroid dependence and once again diagnosed with frequent relapse or steroid dependence after completion of immunosuppressive drug therapy (cyclosporine, cyclophosphamide, mizoribine, etc.) (2) Diagnosed with frequent relapse or steroid dependence and once again diagnosed with frequent relapse or steroid dependence during immunosuppressive drug therapy (cyclosporine, cyclophosphamide, mizoribine, etc.) (3) Diagnosed with steroid resistance and diagnosed with frequent relapse or steroid dependence during or after the completion of immunosuppressive drug therapy (cyclosporine or combination of cyclosporine and methylprednisolone, etc.)
C. *Remission*	Negative protein on urine dipstick in the first morning urine for 3 consecutive days.
D. *Steroid sensitivity*	When the daily administration of prednisolone at 60 mg/m^2^/day leads to remission within 4 weeks.
E. *Relapse*	Protein 2+ or above detected by urine dipstick in the first morning urine for 3 consecutive days and prednisolone treatment is required.
F. *Frequent relapse*	Two or more relapses within 6 months after initial remission or 4 or more relapses within any 12-month period.
G. *Steroid dependence*	Two consecutive relapses during the reduction of steroid therapy or within 2 weeks of discontinuation of steroid therapy.
H. *Steroid resistance*	When the daily administration of prednisolone at 60 mg/m^2^/day does not lead to remission within 4 weeks.

### Statistical analyses

The primary aim of this study is to examine the superiority of RTX plus MMF combination therapy compared with RTX monotherapy in extending the duration to treatment failure. Based on a previous study, we hypothesize a 1-year event rate of 40% in the RTX treatment group and expect the RTX plus MMF treatment to decrease that to 20%. The planned sample size is 80 patients: 37 patients in each group will be needed to have 80% power for a log-rank test with a 5% significance level, under an assumption of proportional hazard rates, 3 years accrual, and one-and-a-half years follow-up. To allow for withdrawal of consent after participation in the study or loss to follow-up, we set the study size to 80 participants in total. The power calculation was performed using SAS version 9.3 (SAS Institute Inc., Cary, NC, USA). As a primary analysis, time-to-treatment failure is summarized using the Kaplan-Meier method and results compared using the log-rank test. The hazard ratios with 95% confidence intervals are estimated using Cox proportional hazard model. Secondary endpoints including time to relapse, time to FRNS, time to SDNS, time to SRNS, and B cell depletion period will be analyzed in the same manner as the primary endpoint. Model based analysis will be performed as needed. Relapse rate will be compared by permutation testing. Total steroid dose will be compared with the Wilcoxon test.

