### Procedures

#### Observation period

The observation period is from the date the first dose of RTX is administered (day 1) to the date MMF administration is finished (day 505).

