For complicated FRNS/SDNS patients, long-term treatment and multiple side effects are major issues. Current immunosuppressants such as calcineurin inhibitors, cyclophosphamide, mizoribine, and RTX have certainly helped patients, but existing treatments are not optimal. If we can demonstrate that MMF is safe and able to attain the long remission used for maintenance therapy after RTX, we will reduce the total dose of steroids, calcineurin inhibitors, and improve the quality of life in patients with complicated FRNS/SDNS. However, a limitation is that we cannot know the long-term prognosis of patients just by this trial, of which the observational period is just 18 months. In addition, MMF may not be curative like other existing treatments. Therefore, we must investigate the long-term prognosis of MMF in conjunction with RTX treatment while the discovery of treatments with a curative mechanism is also anticipated.

In conclusion, we conduct a multicenter, double-blind, randomized, placebo-controlled trial to evaluate the efficacy and safety of MMF after RTX therapy in children with complicated FRNS/SDNS. Results from this study may impact the management of pediatric complicated FRNS/SDNS patients. Improvement in quality of life will be accomplished by long-term remission, which should be of great benefit to both children with complicated FRNS/SDNS and their families.

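### The 80% power rests on 1.5 to 4.5 years at risk per patient, but the observation period ends at day 505 and no passage says whether later failures count

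*Protocol article*

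**What the plan says.** All references are to the protocol article.

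- **Statistical analyses, effect:** "we hypothesize a 1-year event rate of 40% in the RTX treatment group", with 20% expected under RTX plus MMF.
- **Statistical analyses, size:** "37 patients in each group will be needed to have 80% power for a log-rank test with a 5% significance level". The timing behind that number is then given in these words: "under an assumption of proportional hazard rates, 3 years accrual, and one-and-a-half years follow-up". For withdrawals and losses, "we set the study size to 80 participants in total".
- **Observation period:** it runs from the first rituximab dose (day 1) "to the date MMF administration is finished (day 505").
- **Discussion:** as a limitation, the trial cannot show long-term prognosis, "of which the observational period is just 18 months".
- **Table 1 (Visit schedule):** after day 505 there is a separate follow-up column, headed 36/48 months or trial discontinuation. Relapse evaluation and urinalysis are marked in it.
- **Outcomes:** time to treatment failure is defined without a time limit or censoring date.

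**The concern.** In a log-rank design, power depends on the number of failures. Accrual time adds failures only when early entrants stay under observation until a common closing date. When every patient has the same fixed window, the length of accrual adds nothing.

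The sample-size statement uses the first kind of design. The Observation period section and the Discussion describe the second. The two differ by about a third of the expected failures, so the power claimed for the primary superiority test may not be a property of the trial as described. Readers of a non-significant result would judge it against the stated 80%.

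**Working it through.** **Inputs (Statistical analyses; Observation period).** One-year failure rates 40% and 20%; 5% level, taken as two-sided because the article does not say; 37 per group needed, 80 enrolled, 1:1; window ending at day 505, i.e. 505/365.25 = 1.383 years. Constant hazards are assumed. Dropout is ignored because no rate is given.

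**Step 1: hazards and failures needed.**
- Control: −ln(0.6) = 0.511 per year. MMF: −ln(0.8) = 0.223 per year.
- Hazard ratio (HR): 0.223/0.511 = 0.437, with ln = −0.828.
- Schoenfeld: 4 × (1.960 + 0.842)² / 0.828² = 45.8, so about 46 failures.

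**Step 2: reproduce the stated 37.** With uniform accrual over 3 years and 1.5 years' minimum follow-up, the failure probability is 1 − [exp(−1.5λ) − exp(−4.5λ)]/(3λ).
- Control 0.762, MMF 0.478, mean 0.620.
- 45.8/0.620 = 73.8 patients, i.e. 37 per group. (Rounding up to 46 failures first gives 38.)
- With 37 per group, 45.9 failures are expected. Power is 80% by Schoenfeld, and 79% both by a Lakatos-type calculation and by simulation.

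The stated figure is therefore sound on this basis.

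**Step 3: fixed windows.** The failure probability becomes 1 − exp(−λT), and power = Φ(√(failures/4) × 0.828 − 1.96). At day 505 the probabilities are 0.506 and 0.265, mean 0.386.

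| Follow-up | Per group | Failures | Schoenfeld | Lakatos | Simulated |
|---|---|---|---|---|---|
| 3 y accrual + 1.5 y | 37 | 45.9 | 80% | 79% | 79% |
| 3 y accrual + 1.5 y | 40 | 49.6 | 83% | 82% | 82% |
| Fixed, day 505 | 37 | 28.6 | 60% | 58% | 58% |
| Fixed, day 505 | 40 | 30.9 | 63% | 61% | 62% |
| Fixed, 18 months | 37 | 30.3 | 63% | 61% | 61% |
| Fixed, 18 months | 40 | 32.8 | 66% | 64% | 64% |

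Freedman's formula is lower still at day 505 (55% and 59%), but it also does not reproduce 37 on the staggered basis (it gives 42).

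**Step 4: could another convention yield 37 from a fixed window?** No. By the three formulas, a two-sided test needs 57–64 per group at 18 months and 60–68 at day 505. A one-sided test needs 46–51 and 48–54. On the staggered basis a one-sided test would need only about 30 by Schoenfeld or Lakatos (34 by Freedman).

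**Step 5: if failures after day 505 count.**
- HR 0.437 undiminished, everyone followed to 36 months: 47.1 or 50.9 failures, power about 81% (37 per group) or 84% (40).
- Hazards equal from day 505, staggered or 36-month follow-up: about 36–41%.
- HR 0.7 after day 505 (an assumption): about 58–62%.
- MMF hazard 0.30–0.35 per year after day 505 (an assumption), 40 per group: about 63–71%.

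**Step 6: effect detectable with 80 patients at day 505.** For 16.5% against 40% at one year, HR = −ln(0.835)/0.511 = 0.353. Expected failures are 40 × (0.506 + 0.221) = 29.1, against 4 × 2.802²/(ln 0.353)² = 29.0 needed. Schoenfeld power is therefore 80%.

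**The case against.** The best answer is that day 505 is never named as the censoring date. The observation period is defined, but the endpoint has no time limit. Table 1 schedules relapse evaluation at 36/48 months, and the Outcomes section diagnoses failure from relapse dates. The Randomization section keeps investigators blinded until follow-up is complete. The rule that ties failure to the observation period governs stopping of study drug, not censoring. The proportional-hazards assumption is stated openly, and on it a fixed 36 months gives at least 80%. A condensed article may also leave censoring rules to documents not shown.

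Much of this stands, and it rules out three stronger readings that a reader might infer:

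- **That the trial simply has about 60% power.** That figure is conditional on censoring at day 505, which no passage fixes.
- **That 80% needs exactly 1.5 to 4.5 years per patient.** A fixed follow-up of about 3 years also reaches it, under undiminished proportional hazards.
- **That the 18 months in the Discussion is an error because 504 days is 16.6 calendar months.** Table 1 runs in 28-day steps that the article calls months, and 18 × 28 = 504.

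The objection does not rescue the statement as printed. The follow-up column lies outside the defined observation period, shows no scheduled visits between day 505 and 36/48 months, and is nowhere linked to the primary analysis. The Discussion's limitation about an 18-month period sits badly with a calculation that averages 3 years at risk. Counting later failures also extends proportional hazards into years without MMF. The article offers no support for that: its Discussion allows that MMF may not be curative, and its Background reports frequent relapses after cyclosporine is withdrawn.

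Leaving a censoring rule to an analysis plan would be no fault. The point here is a power figure whose stated follow-up basis disagrees with the design described beside it.

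**Conclusion.** The concern holds as an unreconciled follow-up basis for the stated power. A window of about 18 months is the more natural reading of the article, but it is not established.

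- **Censoring at day 505:** the 80% claimed for 37 per group becomes about 58–60%. With all 80 patients it is about 61–63%, on about 31 failures where 46 are needed.
- **Censoring at 18 months:** about 61–66%.
- **Failures to 36/48 months counted:** about 80% or more, but only with the full effect persisting off drug. It falls to about 36–41% if the hazards become equal at day 505, which is the extreme case; partial persistence lies between.

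These figures assume a two-sided 5% test, constant hazards up to day 505 and no dropout. The hazard shape matters somewhat: with no failures in the first 120–180 days and the one-year rates kept, power at day 505 with 80 patients is about 65–71%, still short of 80%.

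**What to change.** State the censoring date of the primary endpoint, and make the Observation period, Table 1, Statistical analyses and Discussion agree with it. Then restate the power on that basis.

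- **If the date is day 505:** drop accrual time from the justification. State about 46 failures needed, about 31 expected with 80 patients, and power about 61–63% for 40% against 20%. Add that 80% power applies only to about 40% against 16.5% at one year (HR about 0.35, by Schoenfeld's formula).
- **If failures to 36/48 months count:** say so, state that the 80% assumes the full treatment effect persists after MMF stops, and give the power if it does not.

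The cost is a few sentences and, on the first branch, a less favourable stated power. No extra enrolment and no change to clinical management are needed.

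### The stated 80% power relies on follow-up of up to 4.5 years at an unchanged hazard ratio, while observation is said to end with MMF at day 505 and the primary comparison has no window

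*Protocol article*

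**What the plan says.** Four parts of the protocol article bear on how long patients count in the primary comparison.

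- **Statistical analyses, method.** For the primary endpoint, "time-to-treatment failure is summarized using the Kaplan-Meier method and results compared using the log-rank test"; a Cox model supplies the hazard ratio. Neither this section nor Outcomes sets a time limit.
- **Statistical analyses, sample size.** The authors write "we hypothesize a 1-year event rate of 40% in the RTX treatment group"; adding MMF is assumed to bring this down to 20%. They conclude that "37 patients in each group will be needed to have 80% power for a log-rank test with a 5% significance level". The calculation was made "under an assumption of proportional hazard rates, 3 years accrual, and one-and-a-half years follow-up". For withdrawals and losses, "we set the study size to 80 participants in total".
- **Observation period.** It runs from the first rituximab dose "to the date MMF administration is finished (day 505"). The Discussion gives the length of observation as 18 months and names this as the reason why long-term prognosis will remain unknown.
- **Visit schedule, Table 1.** A separate follow-up period after day 505 is headed "36/48 month Clinical trial discontinuation", and relapse evaluation is ticked there.

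**The concern.** Treatment failure is diagnosed from relapse dates, so relapses recorded after day 505 could enter the primary endpoint. The text describes a trial that stops observing at day 505 or 18 months, but the sample size appears to count patients for up to 4.5 years. The two cannot both describe the primary analysis.

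The choice matters in two ways. If the observation period governs, there are far fewer events than the power statement needs. If the longer follow-up governs, much of the information comes from time when the MMF arm is no longer on MMF, and the stated power then needs the same hazard ratio off drug as on it. In that case the single Cox hazard ratio would also depend on how long patients happened to be followed.

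**Working it through.** **Inputs from Statistical analyses.** One-year event rates 40% and 20%; 5% level (taken as two-sided, which is not stated but reproduces the result); 80% power; 3 years accrual plus 1.5 years follow-up; 37 per group needed, 80 enrolled. **From Observation period.** Day 1 to day 505, so 504/365.25 = 1.38 years.

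**1. Hazards and events.** With exponential times, the control hazard is −ln 0.6 = 0.511 per year and the MMF hazard −ln 0.8 = 0.223 per year. HR = 0.223/0.511 = 0.437, and ln HR = −0.828. Schoenfeld events: 4 × (1.960 + 0.842)² / 0.828² = 45.8, i.e. 46.

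**2. The plan's own figure.** With uniform entry over 3 years and closure 1.5 years after the last entry, each patient is followed 1.5 to 4.5 years. The event probability is 1 − (e^(−1.5λ) − e^(−4.5λ))/(3λ), which gives 0.762 for control, 0.478 for MMF and a mean of 0.620. N = 45.8/0.620 = 73.8, i.e. 74, or 37 per group. The stated size is reproduced, with power 80.1%.

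**3. The observation period instead.** For fixed follow-up the event probability is 1 − e^(−λt). Power is Φ(0.828 × √events / 2 − 1.960).

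| Follow-up per patient | Control | MMF | Mean | N for 80% | Events, 80 patients | Power, 80 patients |
|---|---|---|---|---|---|---|
| To day 505 | 0.506 | 0.265 | 0.385 | 119 | 30.8 | 63% |
| 18 months | 0.535 | 0.284 | 0.410 | 112 | 32.8 | 66% |
| 1.5–4.5 years | 0.762 | 0.478 | 0.620 | 74 | 49.6 | 83% |

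Simulated log-rank tests to day 505 give 61–62% with 80 patients, and 79.6% with 60 per group. A uniform 3 years per patient would give N = 72, close to the stated 74, but that is not the stated design and it also runs well past day 505.

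**4. Share of events after day 505.** On the plan's own assumptions it is 1 − 0.385/0.620 = 38%.

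**5. Sensitivity to what happens off drug.** The article gives no hazard after MMF stops, so the values below are assumptions. Simulation: 80 patients, exponential hazards, no dropout, censoring uniform on 1.5–4.5 years, HR 0.437 to day 505 and then as shown. Ranges span repeated runs.

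| Assumed HR after day 505 | Power | Average HR |
|---|---|---|
| 0.437 (full effect persists) | 82–83% | 0.42–0.44 |
| 0.7 | 62–63% | 0.52–0.53 |
| 1.0 (effect ends with drug) | 38–41% | 0.62–0.63 |
| 1.5 (rebound) | 15–16% | 0.78–0.79 |

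**6. Break-even.** Stopping the analysis at day 505 keeps the hazard ratio near 0.44 with 61–63% power. Full follow-up gives about the same power at an off-drug HR of 0.7, which retains ln 0.7/ln 0.437 = 0.357/0.828 = 43% of the effect on the log scale.

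**The case against.** The strongest reply is that only a condensed article is at hand, and a censoring rule for a log-rank test is normally left to the full protocol or SAP. That stands for the bare omission: a missing cut-off date would not be a point by itself. It does not cover a printed sample size whose follow-up disagrees with the printed observation period.

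A reader might infer that the primary analysis is planned to run to month 36/48. The article does not say so. The defined observation period and the Discussion's 18 months point the other way, as does the drug-discontinuation rule, which refers to failure within the observation period. The 36/48-month column stands under its own heading, and the table does not settle whether it means time per patient or calendar time. The document is in conflict with itself; it does not plainly commit to the longer analysis.

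A reader might also infer that proportional hazards must fail once MMF stops. That is not shown. The Discussion concedes only that MMF may not be curative; if the effect persists unchanged, there is no dilution and the stated power holds. Even under waning, the log-rank test keeps its validity under the null. What changes is its power and the meaning of one hazard ratio. Comparing a fixed treatment course over all follow-up is also a legitimate question.

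Finally, a day-505 window does not win everywhere. Full follow-up has the higher power once more than roughly 40–50% of the log hazard ratio persists off drug.

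**Conclusion.** The point holds as an unreconciled conflict between the sample-size follow-up and the observation period, with no stated window for the primary comparison to resolve it. If day 505 governs, power with 80 patients is about 61–63%, not 80%, on about 31 events. If follow-up of 1.5–4.5 years governs, about 80% is reached only when the full effect outlasts the drug; at assumed off-drug hazard ratios of 0.7, 1.0 and 1.5 it is about 63%, 38% and 15%, and the estimated hazard ratio moves from 0.44 to about 0.52, 0.63 and 0.78. Neither reading supports the stated power without that extra assumption.

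The day-505 figures rest on the plan's own event rates, exponential times and no dropout. The off-drug figures rest in addition on hazard ratios that the article does not supply and should be read as a range.

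**What to change.** Before unblinding:

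1. State the primary-analysis window in Statistical analyses and reconcile it with Observation period, Table 1 and the 18 months in the Discussion. Day 1 to day 505 in all randomised patients, including those who stop study drug early, with administrative censoring at day 505, matches the defined observation period and the maintenance aim.
2. Replace the 80% power statement with the figure for that window: about 61–63% with 80 patients. Restoring 80% would take about 119–120 patients.
3. Report failures after day 505 as a secondary analysis, with Kaplan-Meier curves over full follow-up and separate hazard ratios before and after day 505.
4. If the longer window is preferred, state the assumption of a persisting effect and show the power under waning.

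The cost of steps 1 to 3 is wording, about 31 primary events instead of about 50, a less favourable stated power, and lower power than full follow-up if more than roughly 40–50% of the log hazard ratio persists off drug. The off-drug question becomes secondary.
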